## Abstract

**Background:**

Knee osteoarthritis (OA) is a leading cause of global disability. The understanding of the role of psychosocial factors in knee OA outcomes is still evolving particularly in an Asian context. The primary aim of this study is to explore psychosocial factors that prognosticate short and long-term clinical outcomes, productivity, and healthcare utilization in patients with knee OA. Secondary aims are to explore the mediation and directional relationships and the role it plays in predicting the discordance between self-reported measures (SRM), physical-performance measures (PPMs) and objective clinical parameters.

**Methods:**

A multi-centre prospective cohort study of community ambulant knee OA patients seeking treatment in the tertiary healthcare institutions in Singapore will be conducted. Patients with secondary arthritis, significant cognitive impairment, severe medical comorbidities or previous knee arthroplasty will be excluded. Primary clinical outcome measure is the Knee injury and OA Outcome Score-12 (KOOS-12). Baseline characteristics include sociodemographic status, arthritis status including symptom duration and radiographic severity, comorbidities and functional status through Charlson Comorbidities Index (CCI), Barthel Index (BI) and Parker Mobility Score (PMS). Psychosocial variables include social support, kinesiophobia, negative affect, self-efficacy, injustice, chronic illness shame and the built environment. Clinical outcomes include quality of life, physical performance, global assessment, satisfaction and physical activity levels. Productivity and healthcare utilization will be assessed by a modified OA Cost and Consequences Questionnaire (OCC-Q) and the Work Productivity and Activity Impairment Questionnaire (WPAI). Variables will be collected at baseline, 4, 12 months and yearly thereafter. Regression, mediation and structural equation modelling will be used for analysis.

**Discussion:**

Results will allow contextualization, identification, and phenotyping of the critical (and potentially modifiable) psychosocial parameters that predict positive clinical outcomes in the OA population to guide optimization and refinement of healthcare and community. This will facilitate: 1. identification of high-risk knee OA subpopulations that will likely experience poor outcomes and 2. formulation of targeted multidisciplinary comprehensive approaches to address these psychosocial factors to optimize non-surgical treatment care, maximize functional outcomes and create more value-based care model for knee OA.

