### Sample size calculation

Sample size was estimated using G*Power 3.1.9.2. With a small effect size of 0.05, 0.05 type I error, 0.95 power of study and 10 predictive factors to be included into the model, the study will need to recruit 262 subjects. The final estimated sample size will be 420 cases after considering 20% attrition rate at each time point [(262 × 0.2) × 3 + 262] up to 2 years. Recruitment will be continued through the entire period to maximize statistical power.

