#### Prognostic factors that influence the rehabilitation outcomes

Linear regression modelling will be used to investigate the factors that influence the knee function of the patients. Simple linear regression will be used to explore the variables which significantly predict the outcome, and stepwise variable selection method will be used to build the multivariable models. Multicollinearity and interaction terms of the final model will be checked, and heteroscedasticity. The model fit will be checked and assessed using Hosmer-Leme show goodness of fit test. In secondary analysis, mixed effect generalized linear models will be used to explore the changes in outcomes across time as well as the factors predicting the outcome of interest. Mediation analyses will also be conducted to explore the potential mediating psychosocial factors between predictors with clinical outcomes. Structural equation modelling (SEM) cross lagged analysis, an analytical strategy used to describe reciprocal relationships or directional influences, between variables over time, will be used to estimate the directional effects of various psychosocial factors at different time points. Statistical significance will be denoted as *p* < 0.05.

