Results from this study can be used in several ways. Firstly, it can help raise awareness among clinicians who manage patients with knee OA to identify high risk knee OA subpopulations that will likely experience poor outcomes based on pre-existing factors. This would allow them to address these factors and potentially formulate targeted approaches to address these psychosocial factors to optimize non-surgical treatment care, maximize functional outcomes and reducing/delaying the need for expensive surgery. Secondly, the results will inform the development of holistic biopsychosocial integrated multidisciplinary care models that specifically targets high-risk population groups to intervene on prognostic psychosocial factors to optimize outcomes. Results can also be used to augment existing clinical practice guidelines and promote cross-disciplinary training and collaboration to further support integrated care models.

For this study, recruitment will primarily be centred around the tertiary hospitals as patients presenting to the hospital are more likely to be experiencing more symptomatic and debilitating knee OA with the corresponding associated psychosocial factors. This will allow for relationships between psychosocial factors and outcomes to be more clearly established through a well-defined hospital-based cohort. In the next phase upon completion of this study, there are plans for subsequent phases of the cohort study to be expanded further downstream to primary care and the community and to explore other psychosocial factors that emerge over time as part of the larger effort to develop a comprehensive biopsychosocial understanding of knee OA.

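### The results are meant to point to high-risk subpopulations, but the linear model is built by stepwise selection and its only named fit test cannot show predictive value

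*Protocol article*

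**What the plan says.** The Discussion paragraph of the Abstract lists, as the first thing the results will make possible, "identification of high-risk knee OA subpopulations that will likely experience poor outcomes". The section Discussion and conclusion repeats this for clinicians, who are to "identify high risk knee OA subpopulations that will likely experience poor outcomes based on pre-existing factors", and goes on to care models aimed at such groups.

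The analysis is set out under Prognostic factors that influence the rehabilitation outcomes. It starts from screening: "Simple linear regression will be used to explore the variables which significantly predict the outcome". Stepwise selection then builds the multivariable linear model of knee function, and p < 0.05 denotes significance. Multicollinearity, interactions and heteroscedasticity are to be checked, and fit is to be judged by the Hosmer-Lemeshow test. Mixed models, mediation analysis and cross-lagged structural equation models follow.

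The Sample size calculation reads "With a small effect size of 0.05, 0.05 type I error, 0.95 power of study", with "10 predictive factors to be included into the model". It gives 262 patients, raised to 420 for attrition. The primary outcome is KOOS-12, a score. The article gives no value of it that counts as a poor outcome.

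**The concern.** Saying who is likely to do badly is a statement about prediction. The stated route tests whether coefficients differ from zero. These are different questions: with a few hundred patients, a factor can be clearly significant and still leave the outcomes of patients with and without it largely overlapping.

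Two features of the stated method make this more than missing detail. First, the one fit test named does not belong to the model. Hosmer-Lemeshow compares observed and expected event counts in groups of predicted risk, so it needs a binary outcome. Applied to a linear KOOS-12 model it says nothing about explained variance or separation. Second, screening and stepwise selection keep the variables that look strongest in the data at hand, so fit measured in those same data is too good.

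At stake is the use of the results. Care models could be directed at groups defined by factors that separate outcomes only weakly, with the model's apparent fit hiding this.

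**Working it through.** **1. Reproduce the plan's sample size.** Inputs from Sample size calculation: effect size 0.05 (read as Cohen's f²), α = 0.05, power 0.95, 10 predictors. For the two-sided test of one coefficient, use the noncentral F with 1 and N − 11 degrees of freedom and noncentrality f² × N. This gives N = 262 with power 0.9501, as stated. The omnibus test of all ten predictors would need 497. Attrition: 262 + 3 × (262 × 0.2) = 419.2, stated as 420. The study is therefore sized for a single factor.

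**2. Convert the sized effect.** Partial R² = f²/(1 + f²) = 0.05/1.05 = 0.0476, so r = √0.0476 = 0.218. Knowing the factor reduces the outcome SD to √(1 − 0.0476) = 0.976 of its value.

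**3. How well does one such factor separate outcomes?** Assumptions: factor and outcome are bivariate normal with r = 0.218 (2 million simulated pairs), and the poor-outcome share is varied because the article gives none.

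| Share counted as poor | AUC | Poor in factor's top quarter | Poor in the rest |
|---|---|---|---|
| Worst 25% | 0.605 | 34.3% | 21.9% |
| Worst 33% | 0.601 | 43.5% | 29.5% |
| Worst 50% | 0.599 | 61.2% | 46.3% |

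**4. What is the weakest factor that passes p < 0.05?** Smallest significant partial R² = t²/(t² + N − 11), with t the 97.5% point on N − 11 degrees of freedom.
- N = 262: 1.969²/(1.969² + 251) = 1.5%, AUC about 0.56.
- N = 336 (420 × 0.8, the first follow-up): 1.967²/(1.967² + 325) = 1.2%.
- N = 420: 1.966²/(1.966² + 409) = 0.9%, AUC about 0.54 to 0.55.

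**5. Several factors together.** For k independent factors, each with f² = 0.05, R² = 0.05k/(1 + 0.05k). With the worst 25% counted as poor:

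| k | R² | AUC | Poor in top quarter of the combined score | Poor in the rest |
|---|---|---|---|---|
| 3 | 13.0% | 0.67 | 40.9% | 19.7% |
| 5 | 20.0% | 0.71 | 45.2% | 18.3% |
| 10 | 33.3% | 0.78 | 52.5% | 15.8% |

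These are ceilings. They assume uncorrelated factors and known coefficients.

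**6. Size of the optimism.** Assumed for illustration: 25 independent candidates, of which 3 are real at f² = 0.05 (true R² 13.0%), univariable screening at p < 0.05, then backward elimination at p < 0.05, 1,500 repetitions.

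| N | Mean apparent R² | Mean R² in new patients |
|---|---|---|
| 262 | 15.1% | 9.6% |
| 336 | 14.8% | 10.6% |
| 420 | 14.4% | 11.2% |

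Apparent fit lies above even the true R² of 13.0%, while performance in new patients lies below it.

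**The case against.** The strongest reply has four parts.

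- **High-risk identification is a downstream use.** Study aims sets the primary aim as identifying prognostic factors, and regression coefficients address that aim. The Abstract presents the high-risk use as something the results will facilitate. This stands, and it limits the weight of the point.
- **Performance measures may sit in a fuller plan.** The article condenses the protocol, and Study design says a framework for best practice in prognostic research was used. This also stands, so silence on AUC, calibration or validation is not held against the plan. The point rests on what is written: a selection route that inflates fit, and a fit test that does not suit the model.
- **One factor is the weakest case.** The plan foresees a ten-predictor model, and a profile of several factors can separate much better, as step 5 shows. Moreover, f² = 0.05 is the effect the study is powered to detect, not a forecast, and it is a partial effect that step 3 treats as a simple correlation. All true. But whether the final model comes near the ceilings is what the stated check cannot show.
- **The plan does more than test at p < 0.05.** It checks model assumptions and adds mixed, mediation and structural equation models. A reader might infer that it stops at significance, and that would be too strong. None of these additions, however, measures predictive performance.

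**Conclusion.** The point holds as a mismatch between the stated use and the stated model building and fit check. At the sized effect, one significant factor has an AUC of about 0.60, and this barely moves across the three assumed poor-outcome shares. The differences between its top quarter and the rest are 12 to 15 percentage points. Combined factors could reach AUC 0.67 to 0.78 at best. In the illustrative simulation, selection raises apparent R² to 14 to 15% against 10 to 11% in new patients.

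The AUC figures rest on bivariate normality and assumed shares. The optimism figures rest on an assumed 25 candidates with 3 real effects.

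A reader might infer that the study would label individual patients and misclassify most of those it flags. The article does not support that. It speaks of subpopulations and plans no score or labelling rule. Moreover, the statement depends on the cut-off: with the worst 25% as poor, 66% of the top quarter do not do badly, but with the worst 50% as poor, 61% do. Nor is the primary aim of finding associated factors undermined by this point.

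**What to change.** In the section on prognostic factors:

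1. Replace the Hosmer-Lemeshow check for the linear KOOS-12 model with R² and calibration slope on the continuous score. Correct both for optimism by bootstrap, repeating every screening and selection step in each bootstrap sample.
2. Report the corrected gain in R² when the psychosocial factors are added to the clinical baseline variables.
3. Word conclusions as association, and claim high-risk identification only as far as the corrected performance supports it.

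AUC is optional, and only if a poor-outcome cut-off on KOOS-12 is fixed in advance. Otherwise the score should not be dichotomised for this purpose.

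No new data are needed. The cost is extra analysis work, including combining the bootstrap with the planned multiple imputation, and possibly a less favourable headline if corrected performance is weak.

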**Ethics and dissemination:**

The study has been registered under clinicaltrials.gov registry (Identifier: NCT04942236).

## Background

Based on the global burden of disease study, musculoskeletal (MSK) disorders account for the largest cause of disability worldwide [1]. In particular, osteoarthritis (OA) alone is the 3^rd^ most rapidly rising condition associated with disability [2]. 528 million people worldwide suffer from symptomatic and activity-limiting OA affecting quality of life, sleep and mood [3]. Risk factors for knee OA can be divided into modifiable and non-modifiable risk factors [4]. Non-modifiable risk factors include age, gender, ethnicity, genetics and joint-level factors (joint alignment, previous injury). Modifiable risk factors include weight, occupation, sports and joint alignment [5]. These factors work together to influence the progression of disease and its accompanying functional limitations.

Treatment algorithms and disease prognosis for knee OA have traditionally been viewed through a biomedical lens [6]. However, this approach is now considered outdated and missing many important factors [7]. Patients who present with similar radiographic joint abnormalities could have significant differences in how they experience their OA pain with evidence showing a discordance between objective clinical and radiological markers and self-reported pain and disability [8]. Large scale prognostic studies have focused on predominantly biomedical factors but failed to predict pain and functional impairment with high levels of certainties [9]. Pain itself is a complicated phenomenon, manifested and potentially modified by a complex interplay of neuropathic, physiological, psychological, genetic, social and personal factors, each contributing to a multifactorial experience of pain and hence challenges in empirical measurement [10–13]. These intricacies of pain experiences call for a wider approach toward the understanding and treatment of pain by incorporating a psychosocial perspective.

Mounting evidence has emerged that posits that psychological and social outcomes caused by direct or indirect effects of OA pain can also worsen disease trajectory [14]. The pathway between pain and psychological symptoms can be reciprocal and potentially causational [15–17]. Prolonged pain experiences can lead to negative psychological outcomes, and vice versa. A recent longitudinal study found that greater perceived OA pain and dysfunction at baseline is found to be associated with a higher incidence of depression at follow up [18]. Systematic review-level evidence has also identified that anxiety and depression symptoms in patients with OA are associated with poor healthcare outcomes, including increased doctor visits, healthcare utilisation, medication prescription, poor surgical outcomes and post-surgical pain [14]. Luong et al. explored the social factors in OA, highlighting the overall paucity of research in this area with the research mainly focusing on social position (education, income and occupation) and proposed a framework to guide future research [19].

Despite all this, the understanding of the role of psychosocial factors in knee OA outcomes is still early and evolving with a paucity of research involving psychosocial outcomes in patients with knee OA particularly in an Asian context. Existing large prospective cohort studies such as the Multicentre OA Study (MOST), OA Initiative (OAI), and the Chinese Primary Knee OA Progression Cohort (CPKOPC) focused mostly on the biological rather than psychosocial factors [20, 21]. A cohort study to identify critical psychosocial factors that predicts the disease trajectory of this Asian patient population, in closer alignment with patient expressed needs to reduce inequities by focusing on care dimensions beyond the biomechanical lens [22] and guide the optimisation and refinement of existing services.

### Study aims

The primary aim is to identify critical psychosocial factors that prognosticate short and long-term clinical outcomes, productivity, and healthcare utilization in patients with knee OA.

The secondary aims areTo explore the mediation and directional relationship between the psychosocial factors with clinical outcome, productivity, and healthcare utilization outcome to support the development of a conceptual frameworkTo explore discordance between self-reported measures (SRM), physical-performance measures (PPMs), objective clinical parameters e.g. radiographic severity in knee OA and the extent to which psychosocial factors predicts the extent of discordance

## Methodology

### Study design

The Singapore KneE OA CoHort (SKETCH) study is a multi-centre, prospective cohort study. The reporting of the study will follow the Strengthening the Reporting of Observational Studies in Epidemiology (STROBE) guidelines [23]. The Prognostic Research Strategy (PROGRESS) framework was used to incorporate best practices for prognostic research as part of this study protocol [24].

### Study population and setting

In this first phase, patients with knee OA in Singapore seeking medical care from tertiary hospitals and institutions will be recruited. The recruitment locations of the study will primarily be recruited from the outpatient orthopaedic surgery and physiotherapy departments. A second phase is planned to be conducted among patients within primary care and the community.

### Recruitment

Patients who satisfy the inclusion criteria outlined in Table 1 will be recruited. Participants will be identified and recruited with a dual-pronged recruitment strategy. First, research coordinators will conduct a pre-screening of the patients list using the institutions’ appointment and/or medical record systems to identify eligible patients who will be attending the orthopaedic or phsyiotherapy clinic for the day. Second, study site collaborators and their clinical teams, guided by the study inclusion and exclusion criteria will support recruitment by identifying potentially appropriate patients and proactively referring them to the study team. Delegated research coordinators will approach the patients who meet at the outpatient clinics and explain the study’s objectives to the patients. The research coordinator will obtain consent from the patient and offer to administer the questionnaire with the patient at their preferred time and location, or for the patient to complete the questionnaires independently.

**Table 1 Tab1:** Inclusion and exclusion criteria

Inclusion criteria	Exclusion criteria
NICE Clinical criteria for OA Knee *NICE Clinical criteria for OA knee: patient is 45 or over and has activity-related joint pain and has either no morning joint-related stiffness or morning stiffness that lasts no longer than 30 min*	Alternative diagnosis to knee OA e.g.: referred pain from hip/spine *If co-existing pathology is present, patient can still be recruited if the predominant symptoms are from the OA knee with documentation of the co-existing pathology*
Independent community ambulators with or without walking aids	Secondary arthritis e.g., inflammatory
	Inability to comply with study protocol e.g.: significant cognitive impairment
	Severe and unstable medical comorbidities significantly impairing activities of daily living and risk of serious adverse events as assessed by a medical specialist (e.g., New York Heart Association (NYHA) class 4 cardiac failure with significantly impaired effort tolerance, stroke with significant residual functional weakness, psychiatric disorders such as psychosis, terminal cancer with a less expectancy of less than 12 months)
	Previous knee arthroplasty (index knee or contralateral knee)
	Pregnant

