** Built environment**	The built environment questionnaire is a 5-item developed by the study team to assess the participant’s perceptions of accessibility of physical facilities and amenities around their place of residence. This was adapted from the International Physical Activity Questionnaire (IPAQ) environmental module [55]. The items are rated from 1 (very strongly agree) to 7 (very strongly disagree)

The choice of PPMs was based on the recommended OARSI performance test for functional testing in OA [35]. Gait speed timed up-and-go, 4-stair climb test and 30-s chair stand were chosen to encompass the key domains of functional activities from sit-to-stand, walking short distances, stair negotiation and ambulatory transitions. The UCLA activity score is a validated score that is recommended for use in patients with hip or knee OA [38].

The Panel on Cost-Effectiveness in Health and Medicine recommends the use of a societal perspective to ensure that potentially important indirect costs such as productivity and caregiver cost would not be omitted [39]. Cost and healthcare utilization data will be collected via hospital administrative databases and patient-reported questionnaires to estimate direct medical, direct non-medical and indirect costs. Indirect costs include health-related productivity loss due to knee OA [40] from absenteeism and presenteeism, measured with the Work Productivity and Activity Impairment Questionnaire (WPAI) [41]. The scope of the cost data collection was based on the validated OA Cost and Consequences Questionnaire (OCC-Q) [42] and adapted to the Singapore context to ensure that all relevant sources of cost were collected.

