#### Outcome measures timepoints

Upon baseline outcome measure taking, participants will be followed up at 4 months, 12 months, and annually after that. To reduce respondent fatigue and keep questionnaire burden to the minimum, psychosocial variables will be administered in two phases (Table 2) with a core set of outcome measures collected at all time points. In addition, certain psychosocial variables eg. built environment, that are not anticipated to change significantly over time will only be taken at baseline (Table 4).

**Table 4 Tab4:** Data collection at different time points

Measure	Baseline	4 month	12 month	24 month

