**Clinical and functional assessment**				
Knee function^a^	✓	✓	✓	✓
Quality of life^a^	✓	✓	✓	✓
Depression and anxiety^a^	✓	✓	✓	✓
Pain experience^a^	✓	✓	✓	✓
Activity level^a^	✓	✓	✓	✓
Dietary behaviours	✓	✓	✓	✓
Global assessment^a^		✓	✓	✓
Satisfaction with treatment^a^		✓	✓	✓
**Healthcare Utilization and Productivity Costs**^a^	✓	✓	✓	✓
**Quality of Care**	✓			

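### Recruiting from the day's clinic list without separating first from return attendance is expected to raise utilization and cost levels, and leaves stage of care free to confound the KOOS-12 estimates in either direction

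*Protocol article*

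**What the plan says.** The Recruitment section gives two routes into the cohort. Coordinators screen appointment or record systems to "identify eligible patients who will be attending the orthopaedic or phsyiotherapy clinic for the day". Clinical teams also help by "identifying potentially appropriate patients and proactively referring them to the study team". The target population, under Study population and setting, is broad: "patients with knee OA in Singapore seeking medical care from tertiary hospitals and institutions will be recruited".

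Table 1 has no criterion on first visit, new referral, symptom duration or earlier physiotherapy. The only criterion that directly limits prior knee care is "Previous knee arthroplasty (index knee or contralateral knee").

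Time zero is the baseline questionnaire: "Upon baseline outcome measure taking, participants will be followed up at 4 months, 12 months, and annually after that".

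The baseline variables include symptom duration, Kellgren-Lawrence grade, comorbidity and function. Visit number, first or return status and time since referral are not named.

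The primary aim concerns factors that predict "short and long-term clinical outcomes, productivity, and healthcare utilization in patients with knee OA". The cost paragraph after Table 3 says "Cost and healthcare utilization data will be collected via hospital administrative databases and patient-reported questionnaires", in order to estimate direct and indirect costs. Table 4 lists "Healthcare Utilization and Productivity Costs" at baseline and at every follow-up.

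**The concern.** The sampling unit is in effect a clinic visit. A patient who attends six times while recruitment is open has more chances of being approached than one who attends once. Number of visits is a component of utilization, so selection acts on an outcome named in the primary aim. Physiotherapy clinics, a named source, can bring the same patient back repeatedly. The Discussion acknowledges that hospital patients are more symptomatic, but it does not mention selection by attendance frequency.

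The second issue is the point of entry. The 4-month outcome may follow a first consultation in one patient and the end of a treatment course in another. If first and return attenders differ both in a psychosocial score at baseline and in the improvement still to come, stage of care confounds the prognostic estimate for KOOS-12, the primary outcome. This needs no difference in the psychosocial effect between stages; ordinary confounding is enough.

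**Working it through.** The documents give no visit distribution, approach rate or mix of care stages, so there is no figure of the plan to reproduce on this point. The inputs below are assumptions, shown as ranges.

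**1. Utilization levels**

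Let V be a patient's visits and p the chance of being recruited at any one visit.

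- Chance of entry: π(V) = 1 − (1 − p)^V.
- Ratio of sampled to true mean visits: E[V·π(V)] / (E[V]·E[π(V)]).
- For small p, π(V) ≈ pV, and the ratio tends to E[V²]/E[V]² = 1 + CV².

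With mean 4 and SD 2, 3 or 4, CV is 0.5, 0.75 or 1.0, and the limit is 1.25, 1.56 or 2.00. Taking V as 1 plus a negative binomial count:

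| p | SD 2 | SD 3 | SD 4 |
|---|---|---|---|
| 0.01 | 1.24 | 1.54 | 1.95 |
| 0.30 | 1.11 | 1.22 | 1.34 |
| 0.90 | 1.01 | 1.02 | 1.03 |

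This treats V as a stable patient characteristic. If recruitment visits and later visits share only an underlying patient rate (gamma-Poisson, mean 4, CV of the rate 0.5 to 1.0, compared with everyone who attends at least once), the ratio for later utilization is smaller: 1.20 to 1.61 at p = 0.02, 1.05 to 1.11 at p = 0.5, and about 1.01 at p = 0.9. The direction is the same.

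**2. Visit-biased sampling and a psychosocial slope**

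In a simulation where the psychosocial score and severity both drive visits, the slope was about -0.22 in the full population and -0.220 to -0.228 in the sample (p = 0.05). Over-sampling of frequent attenders alone barely moves the association.

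**3. Stage of care as a confounder of KOOS-12**

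Model: K1 = 0.6·K0 − 0.15·F + g·(first attender) + e. Here K0 and K1 are baseline and follow-up KOOS-12, F is fear of movement in SD units, q is the share of returning patients, d is how much lower their mean fear is, and g is the extra gain still to come in first attenders. Assumed ranges: q 0.3 to 0.7, d 0.2 to 0.5, g 0.3 to 0.5.

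If K0 is unrelated to F and to stage, leaving stage out shifts the coefficient of F by

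g·d·q(1 − q) / (1 + d²·q(1 − q)).

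- q = 0.5, d = 0.5, g = 0.5: 0.0625/1.0625 = 0.059, so -0.15 is estimated as -0.091.
- q = 0.3, d = 0.2, g = 0.3: 0.0126/1.0084 = 0.0125, so -0.15 is estimated as -0.138.
- If returning patients instead have higher fear, d changes sign and the same two cases give -0.209 and -0.162.

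Ranges over the grid, with baseline KOOS-12 always in the model:

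| Fear in returning patients | Fear/KOOS-12 correlation within stage | Their past gain already in baseline KOOS-12 | Estimate of -0.15 |
|---|---|---|---|
| Lower | 0 | no | -0.138 to -0.091 |
| Lower | -0.4 | no | -0.135 to -0.081 |
| Lower | -0.4 | yes | -0.150 to -0.109 |
| Higher | 0 | no | -0.162 to -0.209 |
| Higher | -0.4 | no | -0.165 to -0.219 |
| Higher | -0.4 | yes | -0.173 to -0.236 |

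The overall span is about -0.08 to -0.24. Adding the stage term returns -0.15 in every row, but that is true by construction of the example.

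**The case against.** Enrolling patients already in care fits the stated population, and an inception cohort would be a different design. Nothing here is a contradiction or a miscalculation, and time zero is clearly defined as the date of baseline measurement. That stands: the point concerns the consequences of a design choice.

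The primary aim is prognostic association, not mean cost. This largely stands for sampling by visit, as step 2 shows, and rate ratios are largely spared under a multiplicative patient effect. It does not protect the cost levels the protocol says it will estimate, nor does it deal with confounding by stage.

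The size of the inflation is unknown and can be negligible. This also stands. Near-complete capture removes almost all of it, and selection by clinician referral need not follow visit counts. But capturing nearly every eligible attender is an optimistic assumption for a consented cohort with a target of 420.

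Symptom duration, radiographic grade and baseline utilization are collected and allow some adjustment. Only in part: a patient with ten years of symptoms may be at a first consultation or close to discharge. Baseline utilization is a better proxy, though Table 2 presents it as an outcome.

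A condensed article may leave form fields and covariate lists to the full protocol or analysis plan. That is fair, and the absence of a named field is not itself the fault. The recruitment rule and the start of follow-up are stated choices, and first or return status is best captured at entry.

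**Conclusion.** The point holds as a matter of expected bias. Utilization and cost levels from this cohort are expected to be too high for patients with knee OA seeking tertiary care. The factor ranges from about 1.01 to 1.03 with near-complete capture to about 1.2 to 1.95 with sparse recruitment per visit, under an assumed mean of 4 visits with SD 2 to 4. KOOS-12 prognostic estimates may be confounded by stage of care, with a true -0.15 SD appearing anywhere from about -0.08 to -0.24 under the assumed inputs.

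A reader might go further and infer that the design masks psychosocial effects by pulling harmful factors towards zero. The documents do not support that. It requires returning patients to be less fearful or distressed, whereas return attenders at a tertiary clinic could equally be persistent cases with more distress, and the bias would then exaggerate the effect. Nor do the documents show that utilization is in fact inflated by any given amount, or that the prognostic aim fails. The change is worth making because it is cheap and hard to recover later, not because a large bias has been demonstrated.

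**What to change.** - At entry, record whether this is the first attendance of the current knee episode, and by which route the patient was recruited.
- From the hospital databases already used for costs, extract knee-related attendances in the previous 12 months.
- Include first or return status as a prespecified term in the KOOS-12 models, not subject to stepwise selection, and report results for first attenders separately.
- Present utilization and cost levels for first attenders beside the full-cohort figures. Alternatively, as a sensitivity analysis, weight by the inverse of the number of attendances counted including the recruitment visit, so that the count is never zero. This weight approximates the inverse chance of entry only when the chance per visit is small, and it fits clinician-referred patients less well; say so in the report.

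Eligibility and recruitment stay as they are. The cost is one or two fields at entry, one extract and some extra analysis, with less precision in the subgroup or weighted figures. If 30% to 70% of the 420 are returning patients, first attenders number 420 × 0.7 = 294 down to 420 × 0.3 = 126 before attrition, so their separate results would be supportive.
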